### Interventions

All participants will receive pre-specified good standard care of their diabetic foot ulcers in a multidisciplinary diabetes foot clinic setting, following international guidelines [5] as described in Table 1.

**Table 1 Tab1:** Components of good standard wound care

• Formal assessment of ulcer and surrounding skin	
• Provision of any necessary off-loading	
• Debridement (i) sharp, (ii) other as appropriate (but excluding the use of larvae)	
• Appropriate dressing products	
• Appropriate antibiotic therapy	
• Nutrition and self care	
• Optimal glycaemic control	
• Revascularisation if deemed clinically necessary	
• Continued close observation	

Participants randomised to the intervention group will, in addition, receive a weekly application of the LeucoPatch®. The LeucoPatch® is prepared by centrifuging one (for ulcers ≤ 5 cm^2^) or two (for ulcers > 5 cm but ≤ 10 cm^2^) 18-mL aliquots of the participant’s venous blood according to the instructions for use. The centrifugation yields a tough layer of fibrin, with viable leucocytes and platelets, and this is applied directly to the wound surface using sterile forceps. The wound is then covered with an inert primary dressing, a secondary protective dressing and the ulcerated area protected with appropriate off-loading.

### Study visit schedule (Fig. 2)

After giving written informed consent participants will be seen every 2 weeks during a 4-week run-in period to confirm eligibility. Those fulfilling inclusion and exclusion criteria at the end of the run-in period will be randomised and receive study treatment once weekly for 20 weeks or until healing, whichever occurs first. When a blinded observer has confirmed healing of the target ulcer, the patient will be scheduled for two healing confirmatory visits within the next 4 weeks. If target ulcer healing is confirmed by a blinded assessor at the 4-week confirmatory visit, the participant will enter the follow-up phase of the study, completing follow-up visits at 20 and 26 weeks post randomisation. If the target ulcer remains unhealed after 20 weeks of treatment, the participant will complete follow-up visits at 20 and 26 weeks post randomisation.

An additional study visit 12 weeks after initial healing and a telephone follow-up at 52 weeks after randomisation will be made to collect ulcer status (durability of wound healing) and safety information.

### Outcomes

#### Primary outcome

Comparison of the number (%) of hard-to-heal ulcers that heal within 20 weeks following pre-specified good standard care with the numbers healed following standard care plus the topical application of LeucoPatch® in a multidisciplinary diabetes foot clinic setting.

Healing will be assessed following any necessary debridement and will be defined as complete epithelialisation, which is maintained for 4 weeks. Healing will be confirmed both at the start and the end of the 4-week period by an observer who is blind to randomisation group. The date of healing will be that at which it was first noted by the clinical researcher and confirmed by an observer, blind to the intervention group.

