### Randomisation and blinding

Internet-based treatment assignment will be determined by a computer-generated random code using random permuted blocks of randomly varying size, created by the Nottingham Clinical Trials Unit in accordance with their Standard Operating Procedures. Trial participants will be allocated with equal probability to each treatment arm with stratification by centre, and by ulcer area (≤ 100 mm^2^ versus > 100 mm^2^).

The use of the LeucoPatch® in the intervention group will be apparent to both the participant and health professionals involved in the care of their foot ulcer. The primary outcome will, however, be confirmed by observers blind to randomisation group and all other outcomes will be analysed by researchers blind to randomisation group.

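### Blinded confirmation guards the primary outcome against false healing calls, but not against healing that the clinic misses or calls late differently by arm

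*Protocol article*

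**What the plan says.** Methods, Primary outcome, defines healing as full epithelialisation held for 4 weeks and judged after any debridement needed. It then gives the order of events: "The date of healing will be that at which it was first noted by the clinical researcher". The sentence goes on to require confirmation by an observer blind to allocation. The blinded step is described as follows: "Healing will be confirmed both at the start and the end of the 4-week period by an observer who is blind to randomisation group".

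Study visit schedule has the same sequence: "When a blinded observer has confirmed healing of the target ulcer, the patient will be scheduled for two healing confirmatory visits".

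Randomisation and blinding says that use of the patch "will be apparent to both the participant and health professionals involved in the care of their foot ulcer". The primary outcome is to "be confirmed by observers blind to randomisation group and all other outcomes will be analysed by researchers blind to randomisation group". The Discussion repeats that participant and usual-care team cannot be blinded and offers blinded confirmation as the way to lessen bias.

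Secondary effectiveness outcomes lists time in days to healing by 20 weeks. It also lists change in ulcer area at weeks 4, 12, 16, 20 and 26 from tracings and digital images, measured by a blinded assessor. Nothing says that this measurement feeds the healing call.

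**The concern.** A confirm-or-reject step can correct only one kind of error. If the clinic calls an open ulcer healed, the blinded observer can overrule it. If the clinic does not call a closed ulcer healed, or calls it late, the blinded step as described has nothing to act on.

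That matters when the person making the first call knows the allocation and the threshold for calling differs between arms. The 20-week proportion would then compare calling behaviour as well as healing. Time to healing is more exposed, because no healing can be dated before someone notes it and any systematic lateness goes straight into the outcome. Blinded analysis of the other outcomes does not help, since it comes after the call and date have been recorded.

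**Working it through.** **Is the route open on the text?**

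1. First noting: the clinical researcher (Primary outcome).
2. Knowledge of allocation: apparent to staff caring for the ulcer (Randomisation and blinding). That the clinical researcher is one of them is an inference; the article does not state it.
3. Blinded role in the primary outcome: confirmation, in the Abstract, Study visit schedule, Primary outcome, Randomisation and blinding, and Discussion.
4. Blinded look at every ulcer regardless of the clinic's call: only the area measurement, a secondary outcome with no stated link to the healing call.

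The article therefore describes a check on false positives and none on false negatives or late calls.

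**The plan's own figure.** Inputs from Sample size: control 30%, treatment 48%, alpha 0.05 (taken as two-sided), power 80%, Fleiss correction.

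- Uncorrected n per arm = [1.960 × sqrt(2 × 0.39 × 0.61) + 0.842 × sqrt(0.30 × 0.70 + 0.48 × 0.52)]² / 0.18² = 114.1, rounded up to 115.
- Corrected n = (114.1/4) × [1 + sqrt(1 + 4/(114.1 × 0.18))]² = 124.9, rounded up to 125 per arm, or 250 in total.

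This reproduces the stated 250, which is not in dispute.

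**Shift in the difference.** Let m be the fraction of control healings missed or called after week 20, with none in the other arm. The documents give no value for m, so all values are assumed. Shift = m × 30 points.

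- m = 5%: 0.05 × 30 = 1.5 points.
- m = 10%: 0.10 × 30 = 3.0 points.

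**Effect on the test when there is no true effect.** Both arms truly heal at 30%, with 125 per arm and a two-sided 5% pooled test without continuity correction. Let pc = 0.30(1 − m), d = 0.30m and pbar = (0.30 + pc)/2. Then se0 = sqrt(2 × pbar × (1 − pbar)/125) and se1 = sqrt((0.21 + pc(1 − pc))/125). Rejection = Φ((d − 1.96 se0)/se1) + Φ((−d − 1.96 se0)/se1).

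| m in control | observed control rate | spurious difference | two-sided rejection |
|---|---|---|---|
| 0% | 30.0% | 0 | 5.0% |
| 5% | 28.5% | 1.5 points | 5.8% |
| 10% | 27.0% | 3.0 points | 8.2% |
| 20% | 24.0% | 6.0 points | 18.7% |

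**Direction.** Under the planned 30% versus 48%, the same uncorrected test has 83.5% power at 125 per arm.

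- 10% missed in control: 48 − 27 = 21.0 points, power 93.4%.
- 10% missed in the LeucoPatch arm: 43.2 − 30 = 13.2 points, power 58.3%.

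**Which m is plausible?** With weekly visits a missed call is usually a delay. Assume healings are spread evenly over 20 weeks and every control call comes one week late. Then 1/20 = 5% of control healings cross the cut-off, which is the 1.5-point row, while every control healing time lengthens by 7 days. The proportion moves little; time to healing moves throughout.

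**The case against.** The strongest reply is that much of this is inference. The article never says that nomination is the only way to reach the observer, and never states the clinical researcher's blinding status. Referral is operational detail that an article may leave to the full protocol, and the visit figure is not shown. This stands, so the point must be put as what the article describes, not as what the trial does.

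A reader might infer that the healing date is fixed by an unblinded call alone. The full sentence requires blinded confirmation too, and does not say which date applies if the two differ. On either reading, though, the date cannot precede the first noting.

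A reader might also infer that an ulcer not nominated gets no blinded look. The blinded area measurement contradicts that. What is missing is a stated link from it to the healing call.

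Weekly treatment visits, the exclusion of patients unlikely to manage weekly attendance and close observation as part of care for all participants make long-lasting misses unlikely. This stands and is why the likely size is small. Finally, the Discussion claims only that blinded confirmation reduces bias, which is true.

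**Conclusion.** The point holds in limited form. As described, blinding protects the primary outcome against false healing calls and leaves missed or late calls unchecked. The outcome most exposed is time to healing; the 20-week proportion is affected mainly through healings near the cut-off.

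The size cannot be known from the document. The 1.5 and 3.0 points rest on assumed miss rates of 5% and 10% in one arm and none in the other, at the planned 30% control rate. Larger rates are less plausible given the weekly schedule.

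A reader might conclude that the bias favours the device. The documents do not support that: misses in the LeucoPatch arm would hide an effect, as the 13.2-point case shows. Nor does anything show that differential calling occurred. The article contains no contradiction here; it describes a one-sided safeguard that data already planned could partly complete.

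**What to change.** Leave the primary definition unchanged and add a check from material already collected.

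1. The blinded assessor reads the digital images up to week 20 (weeks 4, 12, 16 and 20) for closure in every patient, whether or not the clinic called healing.
2. Report by arm how many ulcers appear closed but were never nominated.
3. Add a sensitivity analysis that counts these ulcers as healed, restricted where possible to those still closed on a later blinded image such as week 26. That image comes 26 − 20 = 6 weeks after the cut-off, longer than the 4-week maintenance period.
4. For any patient still in follow-up, refer such ulcers to the existing blinded confirmation. Recruitment has closed with 269 randomised, so this may apply to few.

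If the full protocol already provides a scheduled blinded closure check independent of the clinic's call, stating so would settle the point.

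The cost is a little extra image reading and one more analysis. Image closure is a proxy: it does not establish epithelialisation after debridement, or closure maintained for 4 weeks, so it must not replace the primary endpoint. Images are preferred to tracings because clinic staff may make the tracings, which would then not be independent of their judgement.

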#### Secondary effectiveness outcomes

Ulcer-related outcomes:Time (days) to healing by 20 weeksThe incidence of healing within 12 and 26 weeksChange in ulcer area at 4, 12, 16, 20 and 26 weeks (as compared to week 0), as assessed by acetate tracing and digital images, measured by a blinded assessorChange in ulcer healing rate between the run-in period and the first 4 weeks in the treatment periodThe incidence of secondary infectionNumber of days of systemic antibiotic therapy administered for foot ulcer infection during the 20 weeks from randomisationDurability of wound healing 12 weeks after complete wound healing

Patient-related outcomes:The incidence of major (above-ankle) amputation affecting the target limb by 12, 20 and 26 weeksThe incidence of major amputation affecting the contralateral limb by 26 weeksThe incidence of minor (below-ankle) amputation affecting the target limb by 12, 20 and 26 weeksThe incidence of minor amputation affecting the contralateral limb by 26 weeksQuality-of-life measured as using the Short Form 12 questionnaire (SF-12) and EuroQol-5D questionnaire (EQ-5D) at baseline, 12 and 20 weeksPain as assessed by Visual Analogue Scale (VAS)Incidence of new anaemia

Patients enrolled in the study will be asked to keep a patient diary to inform a health economic record by logging information on:Consultations, mode and place of consultations with health care professionals not scheduled for the purpose of the studyUsage of home help or home nursingTime spent travelling for consultations scheduled and not scheduled for the purpose of the studyDirect cost of travelling for consultations scheduled and not scheduled for the purpose of the studyDays off work due to the foot ulcersAssistance from non-health care professionals due to foot ulcers

Centres enrolled in the study will be asked to log:Average time per staff category/grade spent per patient administrating standard care and standard care with the LeucoPatch® used in additionAverage salary and working hours for staff categories involved in the studyCurrent medications, dressings and devices used for the treatment of all patients included in the study as detailed under the study visit schedule

### Health economic evaluation

Specific objectives are to establish the costs of the LeucoPatch® in addition to usual care and assess the cost-effectiveness of the LeucoPatch® in addition to usual care versus usual care alone. The perspective of the health care system (e.g. UK NHS) and personal social services, with consideration of a broader societal perspective which considers the impact on patients and their families will be taken. As the study involves three countries, appropriate consideration, following good practice guidelines [25], will be taken to ensure that resources and costs are appropriately calculated given the potential for differences in resource use between countries. Costs associated with the intervention will be determined by calculating the cost of staff time, materials and other resources involved in providing the intervention. These will be compared with changes in the number of visits to general practitioners, hospital, prescribed medication, and social services’ contacts in the intervention and control groups during the investigation. In addition, should data allow, the costs incurred by patients and their families (e.g. travel, time off work) will be calculated. The costs will be compared with the outcomes generated and a series of incremental cost-effectiveness ratios computed, including a cost/quality-adjusted life year analysis, based on changes in EQ-5D. A series of one-way sensitivity analyses will be undertaken to determine the extent to which baseline findings change in light of parameter variation and a probabilistic sensitivity analysis undertaken to determine the extent to which the intervention can be regarded as representing value for money. Should evidence be found from the within-trial analysis on the short-term effectiveness of LeucoPatch® in addition to usual care compared to usual care alone, a decision analytical model will be developed in order to assess cost-effectiveness over a longer time horizon.

Patients enrolled in the study will be asked to keep a patient diary to inform a health economic record by logging information on:Consultations, mode and place of consultations with health care professionals not scheduled for the purpose of the studyUsage of home help or home nursingTime spent travelling for consultations scheduled and not scheduled for the purpose of the studyDirect cost of travelling for consultations scheduled and not scheduled for the purpose of the studyDays off work due to the foot ulcersAssistance from non-health care professionals due to foot ulcers

Centres enrolled in the study will be asked to log:Average time per staff category/grade spent per patient administrating standard care and standard care with the LeucoPatch® used in additionAverage salary and working hours for staff categories involved in the studyCurrent medications, dressings and devices used for the treatment of all patients included in the study as detailed under the study visit schedule

### Safety and tolerability measures

Safety will be assessed in relation to adverse events (AEs), serious adverse events (SAEs), adverse device effects (ADEs) and serious adverse device effects (SADEs).

AEs will be assessed for relatedness to the device, including device failures, errors or misuse of the device. For the purposes of assessing relatedness, the ‘device’ is defined as the three components of the CE-marked LeucoPatch® system, that is:The LeucoPatch® deviceThe LeucoPatch® needle holderCentrifuge insert

No adverse events are expected as a result of the use of the device.

### Analyses

All analyses will be completed on both the ITT and the PP populations. The primary analysis for outcome will be a logistic regression for the proportions of patients healed within 20 weeks taking into account ulcer area, ulcer depth and ABPI.

All secondary variables will be presented using appropriate descriptive statistics and analysed on the basis of the level of measures and the distribution of scores (where appropriate). Analyses will include survival analysis for time to healing and general linear models for difference in change of pain score; with EQ-5D and SF-12 data presented in line with the conventions for these tools.

Cost-effectiveness and cost-utility analysis will be performed based on the cost-related endpoints collected in the study.

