## Methods

### Design

This is a multicentre, multinational, observer-blind, randomised controlled trial. Patients will be randomised 1:1 to the intervention or the usual-care arm.

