### Sample size

Previous non-controlled LeucoPatch® outcome data suggested a healing rate (intention-to-treat) of 54% during a 20-week follow-up period in a study population similar to this study population. Outcome data from a matched control group as well as from placebo/control groups in other diabetic foot studies with inclusion and exclusion criteria similar to these criteria indicate healing rates between 27 and 32% at 20 weeks’ follow-up, although some authors have reported healing rates below 10%.

A sample size for comparing two proportions with Fleiss continuity correction, based on alpha = 0.05 and beta = 80% and with an outcome rate in the control group of 30% and an improvement of 18 percentage points (i.e. to 48%) in the treatment group gives a sample size of 250 evaluable patients. To allow for 30% dropout a sample size of 350 randomised participants is sought.

As there is uncertainty on both healing rates and dropout rates, the Data Monitoring Committee (DMC) will perform an interim based re-estimation of sample size when 140 randomised patients (70 patients in each group) have completed 20 weeks of follow-up. The sample size re-estimation will be done by comparing 20 weeks’ healing proportions from two groups with Fleiss continuity correction, based on two-sided alpha = 0.04 and beta = 80%, on both the intention-to-treat (ITT) and per-protocol (PP) populations.

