## Discussion

Ulcers of the foot are a major source of morbidity to patients with diabetes and costs to health care economies. Whilst clinicians have a plethora of topical and systemic treatments to choose from, few have been subjected to rigorous evaluation in a blinded randomised trial [6].

Early studies with growth-factor-based [18] methods for producing platelet releasate, platelet gel or fibrin-platelet suspensions have been complex and/or required large blood volumes. The LeucoPatch® device, which produces a patch of fibrin platelets and leucocytes from relatively small volumes of the patient’s venous blood, overcomes many of these problems. Early pilot data suggest improved healing in a group of patients with diabetes with hard-to-heal foot ulcers.

The study population is designed to be as inclusive as possible with the aim of maximising the external validity of any findings. Thus, the intention is to include a large percentage of people with diabetes complicated by ulceration of the foot, including those with all but the most severe peripheral arterial or renal disease. Whilst patients cannot be included if the ulcer is clinically infected at the point of randomisation, should secondary infection be detected during follow-up the patient will not be withdrawn. The population of interest and likely to benefit the most are those who do not heal more than 50% in 4 weeks of observation during best standard care (Table 1), the ‘hard-to-heal’ group. It is for this reason that an initial 4-week observation period is scheduled. Whilst it is not possible to blind either the participant or their usual-care team to the allocated arm of the study, the primary outcome measure (clinical healing) will be confirmed by an observer blind to allocated treatment to reduce the possibility of bias.

The primary outcome measure is healing within 20 weeks of randomisation and the trial also includes a number of secondary outcome measures. Principal among these are rate of change in ulcer area as a predictor of the likelihood of eventual healing, minor and major amputation of the target limb, the incidence of infection and quality of life.

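### The primary logistic model does not adjust for run-in change in ulcer area, a baseline value known for every randomised patient; the analysis is valid, but a modest and conditional gain in precision is left unused

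*Protocol article*

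**What the plan says.** Under Analyses, the primary outcome is to be tested by "logistic regression for the proportions of patients healed within 20 weeks taking into account ulcer area, ulcer depth and ABPI". Three covariates are named, and run-in change in area is not one of them.

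Elsewhere the article shows that this value will exist for everyone:

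- Inclusion criteria and Exclusion criteria: an ulcer qualifies only if its area falls by less than 50% and grows by less than 25% over the 4-week run-in.
- Study visit schedule: patients are seen every 2 weeks during run-in, before randomisation.
- Secondary effectiveness outcomes: one outcome compares the healing rate during run-in with that of the first 4 weeks of treatment.
- Randomisation and blinding: stratification is by centre and by ulcer area at 100 mm², not by run-in change.

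The Discussion uses the 4-week change to define the hard-to-heal group. It also lists, among the secondary outcome measures, "rate of change in ulcer area as a predictor of the likelihood of eventual healing".

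The Sample size section describes an unadjusted calculation: "A sample size for comparing two proportions with Fleiss continuity correction", with "an outcome rate in the control group of 30% and an improvement of 18 percentage points", which "gives a sample size of 250 evaluable patients".

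**The concern.** Run-in change is the direct pre-randomisation record of whether an ulcer was already closing, and the outcome is whether it closes by week 20. Area at randomisation does not carry this information. Take two ulcers of 200 mm² at week 0, one down from 380 mm² (200/380 = 0.53, a fall of 47%) and one up from 165 mm² (200/165 = 1.21, a rise of 21%). Both are eligible, and on area they enter the model as identical.

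If the trajectory is prognostic, two things follow. A chance difference between arms in trajectory stays in the treatment estimate, since neither stratification nor the named covariates deal with it. Outcome variation that could have been explained is also left unexplained, which lowers the power of the primary test. At stake are efficiency and protection against chance imbalance. Bias and validity are not in question.

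**Working it through.** **1. The plan's own figure.** Inputs from Sample size and Design: 30% against 48% healed, difference 0.18, mean 0.39; "alpha = 0.05 and beta = 80" per cent (read as 80% power); two-sided test assumed, because it reproduces the result; "Patients will be randomised 1:1 to the intervention or the usual-care arm".

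Uncorrected n per arm = [1.960 × √(2 × 0.39 × 0.61) + 0.842 × √(0.30 × 0.70 + 0.48 × 0.52)]² / 0.18² = 114.1.

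With the Fleiss correction: (114.1/4) × [1 + √(1 + 4/(114.1 × 0.18))]² = 124.9, so 125 per arm and 250 in total. This matches the article. At 125 per arm, power is 80.0% with the continuity correction and 83.5% without it. No covariate enters, so leaving out run-in change takes nothing from the stated 80%.

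**2. Gain from adding run-in change.** The article gives no prognostic strength, so it is assumed over a range. The logistic Wald test was simulated with 250 patients and 4,000 runs per setting, holding marginal healing at 30% and 48%. Run-in percentage change was taken as uniform over -50% to +25%. The three named covariates were pooled into one score with an assumed odds ratio (OR) of 1.5 per SD, independent of run-in change. Monte Carlo error is about 0.6 points per figure.

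To show what each assumption means, the SD of a uniform variable is its width/√12, so the window spans √12 = 3.46 SD. The odds ratio from one end to the other is then OR^3.46.

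| Assumed OR per SD | OR across the window | Power without term | Power with term | Difference (points) |
|---|---|---|---|---|
| 1.0 | 1.0 | 84.8% | 84.4% | -0.4 |
| 1.2 | 1.9 | 84.8% | 84.8% | 0.0 |
| 1.5 | 4.1 | 85.1% | 86.5% | 1.4 |
| 2.0 | 11.0 | 84.6% | 88.2% | 3.6 |
| 2.5 | 23.9 | 83.6% | 88.9% | 5.3 |
| 3.0 | 45.0 | 84.6% | 91.6% | 7.0 |

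A second simulation, with one normally distributed covariate and no others, gave a 5-point gain (83.0% to 88.1%) at a log-odds slope of 0.85 per SD. Over a uniform window that slope means e^(0.85 × 3.46), about a 19-fold difference in odds.

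**3. Chance imbalance.** The standard error of the difference in mean run-in change between arms is √(2/125) = 0.126 SD. An imbalance of one standard error moves the log odds ratio by about ln(1.5) × 0.126 = 0.05 at OR 1.5, or ln(2.0) × 0.126 = 0.09 at OR 2.0. The design effect is ln(0.48/0.52) - ln(0.30/0.70) = 0.77, so the shift is roughly 7% to 11% of it.

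**4. Room in the model.** Expected healed ulcers are 125 × 0.30 + 125 × 0.48 = 97.5, about 98. With treatment and four covariates at one parameter each, that is 97.5/5, about 19 events per parameter.

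**The case against.** The strongest reply is that nothing here is wrong. A logistic model with three sensible covariates is a valid pre-specified analysis, the sample size was never built on adjustment, and the choice among plausible baseline covariates is a matter of judgement. That stands: this is an improvement to consider and not an error. The article is also condensed, and it does not say that its covariate list is exhaustive.

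Three stronger readings are tempting and are not supported.

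- *A reader might infer that the article itself calls run-in change a predictor of healing.* It does not. The predictor wording in the Abstract and Discussion belongs to a secondary outcome measure, and the area-change outcomes are defined against week 0, after randomisation. Using run-in change as an entry threshold suggests that it is prognostic but says nothing about its strength among those who pass.
- *A reader might infer that power falls short of plan, or that a large gain is available.* Step 1 rules out the first. A gain of 5 points or more needs about a 19-fold difference in odds across a truncated window, and the article offers no evidence for that. Overlap with the named covariates would shrink the gain further.
- *A reader might infer from the 269 randomised, against 350 sought, that power is now short.* The article reports neither the result of the sample size re-estimation nor actual dropout, so this cannot be established.

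Lateness is a fair worry: recruitment has closed, care is unblinded, and an interim comparison was planned. Fixing the term before unblinding and reporting the present model alongside it largely answers this.

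**Conclusion.** The point holds as a missed efficiency gain. Run-in change is complete by design, is not captured by area at randomisation, is not a stratification factor, and is not among the named covariates. Adding it would probably gain between nothing and about 3.5 points of power at 250 evaluable patients, if its odds ratio per SD is 2.0 or less. If it is not prognostic, the loss is within simulation error (84.8% against 84.4%). It would also remove chance imbalance in pre-trial trajectory from the estimate.

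These sizes rest on assumptions that the article neither confirms nor denies: the prognostic strength, a uniform spread over the eligible window, independence from the other covariates, and the planned healing rates. The simulation used percentage change, and the log ratio proposed below was not simulated separately. The planned analysis remains valid and the stated 80% power stands.

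**What to change.** Before unblinding, add one continuous term to the primary logistic model beside ulcer area, ulcer depth and ABPI: log(week 0 area / area at the start of run-in). Report the model without it as a sensitivity analysis. If allocation has already been revealed to those who set the analysis, keep the present model as primary and label the adjusted one as post hoc.

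The cost is one degree of freedom and a conditional odds ratio with a slightly different meaning. No new data, visits or patients are needed.

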### Study setting and participants

Participants will be recruited from specialist diabetes foot care clinics at sites in the UK, Denmark and Sweden.

Eligible participants will be people aged 18 years and over who have diabetes complicated by one or more foot ulcers. In addition, the following inclusion and exclusion criteria will apply:

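### Randomisation is stratified by centre, but the primary logistic model as stated does not include centre, so the primary test is conservative if healing differs between centres

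*Protocol article*

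**What the plan says.** Under Randomisation and blinding, allocation uses "random permuted blocks of randomly varying size" with "stratification by centre, and by ulcer area", the area cut being 100 mm². Under Design: "Patients will be randomised 1:1 to the intervention or the usual-care arm". Participants come from "specialist diabetes foot care clinics at sites in the UK, Denmark and Sweden" (Study setting and participants).

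Under Analyses, the primary analysis is a "logistic regression for the proportions of patients healed within 20 weeks", "taking into account ulcer area, ulcer depth and ABPI". Area therefore appears both in the randomisation and in the model. Depth and ABPI are in the model without having been stratified on. Centre was stratified on and is not in the model. No other section brings centre into the primary analysis, as a fixed effect, a random effect or a stratum.

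**The concern.** Blocking within centre makes the two arms nearly equal in their mix of centres. If centre predicts healing, the treatment comparison then varies less from trial to trial than it would under simple randomisation. A model without centre does not know this. It counts the between-centre spread as noise, so its standard error is larger than the true one and its test rejects less often than the nominal 5% under the null.

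Some difference between centres is plausible. The clinics are in three countries, and several components of standard care in Table 1 (off-loading, dressings, antibiotics, revascularisation) are left to local judgement. At stake is some power for the primary comparison, and a standard error that does not reflect the randomisation used.

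**Working it through.** **1. The plan's own sample size.** Inputs from Sample size: 30% versus 48%, alpha 0.05 (taken as two-sided), power 80% (printed as beta), Fleiss correction.

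- Uncorrected n per arm = [1.96·√(2·0.39·0.61) + 0.8416·√(0.30·0.70 + 0.48·0.52)]² / 0.18² = (1.352 + 0.571)² / 0.0324 ≈ 114.1.
- Corrected n = (114.1/4)·[1 + √(1 + 4/(114.1·0.18))]² ≈ 124.9, so 125 per arm and 250 in total, as stated.

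The formula has no centre term, so nothing in this point alters it.

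**2. Rough size of the standard-error mismatch.** With healing probability p and between-centre SD s on the log-odds scale, the variance of the centre-specific probabilities is about [p(1−p)]²s². Stratified allocation removes that share from the true variance, so true SE / model SE ≈ √(1 − p(1−p)s²). With p = 0.30, p(1−p) = 0.21.

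- s = 0.5: √(1 − 0.0525) = 0.973. Type I error ≈ 2[1 − Φ(1.96/0.973)] ≈ 4.4%.
- s = 1.0: √(1 − 0.21) = 0.889. Type I error ≈ 2[1 − Φ(1.96/0.889)] ≈ 2.8%.

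This is a first-order approximation and assumes perfect balance within centre, so it overstates the effect at large s.

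**3. Simulation at the planned size.** N = 250, healing calibrated to 30% versus 48% overall, blocks of 2 and 4 within centre by area. Assumed, because the article gives no figures: 10 or 25 centres, area log odds ratio 0.8.

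For logistic regression with area but not centre (1,500 runs), the ratio of empirical to model SE under the null, for 10 and 25 centres, was:

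- SD 0: 1.03 and 1.01
- SD 0.5: 1.00 and 0.98
- SD 1.0: 0.93 and 0.91, with type I error 3.0% and 3.3%

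For Cochran-Mantel-Haenszel tests (4,000 runs), power stratified by area only versus by centre and area, for 10 and 25 centres, was:

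- SD 0: 84.2 vs 84.2% and 85.0 vs 83.2%
- SD 0.5: 84.8 vs 85.6% and 85.7 vs 85.0%
- SD 1.0: 86.5 vs 89.9% and 85.8 vs 88.9%, with area-only type I error 4.2% and 3.4%

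**4. Simulation of the proposed model.** N = 269 (the number randomised, from Trial status), the same blocking, and log odds ratio 0.77, from ln(0.48/0.52) − ln(0.30/0.70) = −0.080 + 0.847. The comparison is logistic regression with area, without and with a random centre intercept (2,000 runs).

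| Centres (assumed) | SD | Type I error, without / with | Power, without / with | Gain, points |
|---|---|---|---|---|
| 30 | 0 | 5.3 / 5.3% | 86.1 / 86.5% | 0.4 |
| 30 | 0.5 | 4.7 / 5.0% | 82.6 / 83.9% | 1.3 |
| 30 | 0.8 | 4.5 / 5.8% | 77.5 / 81.4% | 3.9 |
| 15 | 0.8 | 3.4 / 4.5% | 78.6 / 82.0% | 3.4 |
| 30 | 1.0 | 3.4 / 5.2% | 73.0 / 77.9% | 4.9 |
| 15 | 1.0 | 3.8 / 5.2% | 72.1 / 77.4% | 5.3 |

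The Monte Carlo standard error of a type I figure is √(0.05·0.95/2000) ≈ 0.5 points, so 5.8% is compatible with 5%. Power falls down the table because the odds ratio is held fixed within centre, which lowers the overall difference as SD rises. Only the comparison within a row bears on this point. Depth and ABPI were not simulated, so SD here means the spread between centres that remains after the model's covariates.

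**5. One fixed effect per centre.** In the N = 250 setting this gave type I error of 4.9 to 6.3% (10 centres) and 5.6 to 6.1% (25 centres). Part of its apparent power gain therefore comes from a test that rejects slightly too often.

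**The case against.** The strongest reply is that the consequence is conditional. Standard care is specified in common for all participants. The run-in, area limits, perfusion and infection criteria narrow the case mix, and the model already adjusts for three prognostic variables. SDs of 0.8 and 1.0 correspond to latent-scale intraclass correlations of 0.64/(0.64 + 3.29) = 0.16 and 1/(1 + 3.29) = 0.23. Nothing in the article supports values that high. At SD 0.5 (0.07) almost nothing is lost. All of this stands, and it limits the size claimed.

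Adjusting for many small centres can itself cost power. With N = 269 and 30 assumed centres, Cochran-Mantel-Haenszel power by area only versus by centre was 84.7 vs 82.7% at SD 0.3, 81.3 vs 80.8% at SD 0.5, 78.1 vs 79.4% at SD 0.8 and 72.6 vs 76.3% at SD 1.0. This stands against stratifying by every small centre. It does not stand against a random intercept, which cost nothing at SD 0 in step 4.

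The article is a condensed document, and the analysis plan, which is not shown, may handle centre. That is possible. But the article names its covariates, and the list keeps one stratification factor and omits the other. This is more than silence on detail.

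A reader might infer that the stratification is wasted, or that the odds ratio is biased toward 1. Neither follows. Stratified allocation still balances centre whatever model is fitted. The smaller odds ratio without centre is non-collapsibility: it is a different estimand and not a biased estimate.

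**Conclusion.** The point holds as a mismatch between the randomisation and the stated primary model, with a conditional effect on efficiency. If healing differs between centres, the standard errors are too large and the test is conservative. Under 10 to 30 assumed centres, the loss of power is nil at SD 0, about 0 to 1 point at SD 0.5 and about 3 to 5 points at SD 0.8 to 1.0. Type I error at SD 1.0 is about 3 to 4%. The number of centres, the SD, the block sizes and the area effect are all assumptions.

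It would go too far to say that power is in fact lost, because the article gives no between-centre variation. Nor does the omission produce false positives or undermine the stated sample size. The Analyses section leaves the models for the secondary outcomes open, so the point does not extend to them. The change is still worth making, because it costs almost nothing and protects the primary test if centres do differ.

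**What to change.** Before unblinding, state that the primary logistic regression includes centre as a random intercept alongside area, depth and ABPI. Name the fallback in advance: if the model does not converge, pool small centres within country. Avoid a separate fixed effect for each small centre, because that test can be slightly anti-conservative. If the analysis plan already includes centre, it is enough to confirm this and note the difference from the article.

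The cost is one sentence. Centre is known for every participant from randomisation, and the sample size is unaffected. The downside is a slightly more complex model and an odds ratio that is conditional on centre, which the report should say.
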